##### **11.4.2. Interim analysis**

As analysis, listing and tabulating safety endpoints (serious adverse events, adverse drug events and hemorrhagic events) by treatment will be performed for every safety interim review. As an interim analysis for the review of efficacy and safety endpoints, statistical analysis processing will be performed after listing

and tabulating endpoints by treatment. Details will be described in the interim analysis protocol, which will be drafted together by the Statistical Analysis Committee, the Independent Data Monitoring Committee, and the data center by the time of data lock for the first interim analysis.

The interim analysis will be performed by the analysis officers in charge of the interim analysis in the data center. Then the officers and member of IDMC bear the duty to maintain the confidentiality of any information in the review.

### **11.5. Final analysis**

Final analysis will be performed by the data center after full data lock in accordance with the statistical analysis protocol. Results of this analysis will be compiled in the final analytical report and submitted to the principal investigator and each committee member. The statistical analysis protocol will be authored together by the Statistical Analysis Committee and the data center prior to full data lock.

## **12. Case Report Form Data Entry and Submission**

Investigators and subinvestigators will fill out case report form (CRFs) after observing subjects based on the observation schedule. The current study uses an Electronic Data Capture (EDC) system through a special Internet website for CRFs.

Details are described in the *CRF Manual*.

## **13. Data Management**

Data collected through the EDC system will be stored and managed at the study's data center. Management methods will adhere to the system's operational procedures.

## **14. Ethics**

### **14.1. Rules and regulations to be observed**

All staff involved with the study will adhere to the World Medical Association's *Declaration of Helsinki* (amended 10/2008) and the *Ethical Guidelines for Clinical Studies* (fully revised 07/31/2008), as well as the Pharmaceutical Affairs Law and other relevant laws and regulations. All staff will also observe this study protocol.

### **14.2. Subject benefits and drawbacks**

The current study falls within the scope of treatment norms, including tests.

Using cilostazol in combination with antiplatelet agents, which are considered to offer insufficient prophylactic efficacy against ischemic stroke recurrence as monotherapy, may mitigate recurrence risk over the long term. This constitutes a benefit for subjects, who are able to receive a new method of treatment that had not been previously available. Observations of subjects scheduled at regular intervals during the study period also means that patients will be receiving regular treatment and diagnostic attention.

As described above in 2. *Background and Rationale*, concomitant use of aspirin and cilostazol has not been

associated with an increase in hemorrhagic complications. Similarly, concomitant use of the clopidogrel and cilostazol did not result in increased hemorrhagic complications in overseas research on cardiovascular diseases. The same safety is expected with regard to ischemic strokes, but there are no detailed reports available at this time.

#### **14.3. Review and discussion by ethics committee**

According to *Ethical Guidelines for Clinical Studies*, study center directors must request the institution's ethics committee, either established by the director or otherwise, to make a preliminary review of study protocols to ascertain whether or not they adhere to the guidelines, as well as other issues related to appropriate performance of clinical studies. Items must be brought before the committee as necessary.

#### **14.4. Authoring and revision of informed consent forms and written information for subjects**

Investigators must author and revise as appropriate informational documents as well as consent forms in order to obtain consent from potential subjects. Authoring and revision of these documents must comply with the ethical principles of both the *Declaration of Helsinki* and the *Ethical Guidelines for Clinical Studies*.

In accordance with the *Declaration of Helsinki* and the *Ethical Guidelines for Clinical Studies*, informed consent forms and written information for subjects must contain the following items:

- 1) Explanation of the clinical study
- 2) Target diseases and general treatments
- 3) Study objectives
- 4) Explanation of the study drugs
- 5) Study methodologies
- 6) Expected advantages and disadvantages for subjects
- 7) Treatment methods if not participating in study
- 8) Precautions for study participation
- 9) Planned study period and number of subjects
- 10) Study participation and withdrawal
- 11) Study discontinuation and responses
- 12) Offering of information related to study
- 13) Protection of personal information
- 14) Storage, usage methods, and storage period of materials
- 15) Response and compensation if subject health is damaged
- 16) Conflicts of interest and expenses shouldered by subjects
- 17) Study personnel contacts, study doctors, and contact information

#### **14.5. Informed consent**

Prior to any subject participation in study, an investigator/subinvestigator will make a full explanation with informational materials and obtain freely-given consent in writing from the subject himself or herself. Once

the potential subject fully understands the informational materials, both the investigator/subinvestigator who performed the explanation as well as the patient will sign (or print and affix personal seal) and date the consent documents. Next, the investigator/subinvestigator will give a copy of the signed (or printed with seal affixed) consent documents and informational materials to the subject, and store the original document at the study center.

Patients may not participate in this study if it is determined they lack the capacity to make their own judgments. However, if for some reason the patient is incapable of signing forms themselves, an alternate method of identification such as a fingerprint may be used to allow participation.

If significant changes are made to the informational materials, the investigator/subinvestigator will explain their content again to subjects using the updated documents, and obtain freely-given consent in writing for continued participation in the study.

#### **14.6. Privacy protections and subject identification**

All study personnel will strictly protect subject personal information in accordance with the Act on the Protection of Personal Information.

Investigators/subinvestigators will apply a uniformly-determined subject identification code when enrolling patients or when creating CRFs through the EDC system. No personal information which could identify the subject (name, initials, address, telephone number, etc.) will be used. Investigators/subinvestigators will create a chart linking subject identification codes to chart numbers and other personal information of subjects (a subject identification code list), and store this at the study center. Subject identification codes will be of the following format: **study center code (3-digit)—sequential number (3-digit)**. Study center codes will be allocated to each study center by the data center. Subject identification codes will be used to identify subjects when the data center makes inquiries to study centers about data.

### **15. Study Funding and Conflicts of Interest**

This study is performed under contract between the Japan Cardiovascular Research Foundation and Otsuka Pharmaceutical co., Ltd.. In accordance with rules regarding funding transparency and conflicts of interest of related study institutions, academic societies where results may be presented, publishers, and other entities, the Japan Cardiovascular Research Foundation and Otsuka Pharmaceutical co., Ltd. publically disclose the fact that Otsuka Pharmaceutical co., Ltd. is providing funding for this study.

### **16. Study Expenses**

All treatment performed within the scope of the current study is covered by the national health insurance system. No drugs or tests will be used which are not covered by national health insurance. Further, the number of hospital visits and frequency of tests are similar to those under normal treatment, so participating in the current study constitutes no financial burden for subjects.

## **17. Responses and Compensation for Damage to Subject Health**

### **17.1. Responses to damage to health**

The tests and treatments in the study protocol all lie within the scope of normal treatment. Therefore, in the event of any damage to subject health, investigators/subinvestigators will take all appropriate actions, including full treatment, the expenses for which will be fundamentally compensated by insurance as normal medical procedures. In the event of serious damage to health, subjects will receive an explanation of procedures for applying for compensation from The Relief System for Sufferers from Adverse Drug Reactions.

### **17.2. Clinical study insurance**

Otsuka Pharmaceutical co., Ltd. will enroll in clinical study insurance for the entire study organization in order to cover indemnity liability as well as compensatory liability.

## **18. Revision of the Study Protocol**

If revision of the study protocol becomes necessary after initiation of the study, the principal investigator will perform revisions after gaining approval from the Protocol Authoring Committee. If revisions are deemed significant, they must first be reviewed by the ethics committee of the principal investigator's institution.

After revision, the principal investigator will send the revised protocol or details of the revisions to investigators, all committee members, and the data center. Procedures for review of changes at each study center will follow regulations of applicable ethics committees. Finally, investigators at each study center will revise informed consent forms and written information for subjects according to the changes in the study protocol.

## **19. Study Completion and Early Discontinuation**

### **19.1. Study completion at each study center**

When the study concludes at a study center, the investigator will submit a report of study completion to the center director without delay. The investigator will also submit a copy of the report of study completion to the principal investigator.

### **19.2. Study cancellation or discontinuation at each study center**

- 1) Investigators will assess the issue of whether or not to continue the study in any of the following circumstances:
  - iii. Significant information is obtained about study drug quality, safety, or efficacy
  - iv. A determination has been made that study continuation is problematic
- 2) Investigators will cancel or discontinue the study in any of the following circumstances:
  - iii The ethics committee issues an order or recommendation to cancel or discontinue the study
  - iv The ethics committee issues problematic orders for changing the study protocol etc.
- 3) Investigators will inform the principal investigator of any decision made to cancel or discontinue the study as

soon as possible in writing, along with reasons for this decision.

- 4) Investigators will inform subjects of any decision made to cancel or discontinue the study, and arrange for appropriate treatment and post-processing.

### **19.3. Overall completion of study**

Study is complete once all CRFs from all study centers are confirmed. Once the principal investigator receives notification from the data center that all CRFs have been confirmed, he or she will inform investigators and all committee members at each study center that the study has been concluded. Investigators will then notify the director of their institutions and related departments of this in writing.

### **19.4. Early discontinuation of study**

The principal investigator will act accordingly if he or she receives a recommendation from the Independent Data Monitoring Committee to discontinue the study early. If the principal investigator determines not to follow this recommendation, he or she will inform the Independent Data Monitoring Committee of this fact together with the basis for the decision, and discuss the issue.

If the principal investigator determines to follow the recommendation to discontinue the study early, he or she will immediately contact all investigators, committee members, and the data center to inform them of the early discontinuation, reasons for it, and follow-up responses. After being informed of the early study discontinuation, investigators will convey this to subjects along with the reasons for it, and perform appropriate alternate treatments. Finally, investigators will then notify the director of their institutions and related departments of the early discontinuation in writing.

## **20. Storage of Study-Related Materials**

Investigators will store all documents related to the current clinical study (copies of applications and reports, notifications from study center directors, subject identification code lists, consent documents, CRF copies, and other documents or records necessary for ensuring reliability of data) either until discontinuation or the date 5 years following completion, then dispose of the records in a manner that does not compromise personal information.

## **21. Clinical Study Registration**

This clinical study will be registered with UMIN-CTR and ClinicalTrials.gov prior to initiation.

## **22. Authoring of Clinical Study Report, Disclosure of Study Results, and Ownership of Results and Intellectual Property**

The principal investigator and the Steering Committee will summarize the contents of the final analysis report and author a clinical study report encompassing overall conclusions from the study, problematic issues, analysis and discussion of results, and plans going forward from a primarily clinical perspective.

Study results will also be reported as a paper, with authors to be determined together by the principal

investigator and the Steering Committee.

All data and intellectual property (patent rights, utility model rights, and inventions or devices utilizing these rights) generated by the study will be the property of Otsuka Pharmaceutical co., Ltd..

## **23. Procedures for Adverse Events**

### **23.1. Subject-related response**

The investigator/subinvestigator give sufficient medical response to all clinically problematic adverse events related to the study both during and after the subject's study participation. The subject should be informed when treatment for adverse events is required.

### **23.2. Serious adverse event reporting**

#### **23.2.1. Serious adverse events (SAE) requiring immediate reporting**

The following SAEs require immediate reporting:

- 1) All SAEs occurring during the observation period, regardless of their relationship with the study drug.
- 2) SAEs for which causal relationship with study drugs cannot be denied occurring during the course of a follow-up investigation of an adverse event (see 25. *Follow-Up Investigation of Adverse Events*), or an SAE which becomes serious during a follow-up investigation and for which causal relationship with study drugs cannot be denied.
- 3) SAEs occurring after completion of the study period reported to the investigator/subinvestigator by the subject, and for which the causal relationship to the study drugs cannot be denied according to the investigator/subinvestigator.

#### **23.2.2. Immediate reporting procedures**

Reporting will adhere to the following procedures:

- 1) When adverse events corresponding to the previous section occur, the investigator/subinvestigator will immediately input required information into the EDC (CRF) system, which will report relevant information to the study sponsor and Otsuka Pharmaceutical co., Ltd..
- 2) The investigator/subinvestigator will then submit a detailed report about the SAE (onset of which occurred following study drug treatment) to the study center director as soon as possible, using forms required by the institution. The same information will be input into the EDC (CRF) system, which will report relevant information to the study sponsor. Furthermore, the information of DAPT group will be reported to PV department (pharmacovigilance division) in Otsuka Pharmaceutical co., Ltd..
- 3) The investigator/subinvestigator will furnish additional information about the reported SAE (including autopsy reports, terminal stage medical records, or any other information) to the study sponsor, study center director, ethics committee, and Otsuka Pharmaceutical co., Ltd. as requested.

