#### **DAPT group**

One of the following drugs will be administered:

|              |                               |
|--------------|-------------------------------|
| Aspirin:     | 81 or 100 mg/day (once daily) |
| Clopidogrel: | 50 or 75 mg/day (once daily)  |

As a rule, cilostazol (Pletaal OD tablet® & reg.) will be co-administered twice daily at the maintenance dose of 200 mg/day. However, the starting dose can be 100 mg/day, in which case the dose must fundamentally be increased to 200 mg/day within 15 days.

Cilostazol, aspirin and clopidogrel are referred to below as study drugs.

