### 6.3.3. Events

If any event described below occurs, the information below must be reported.

Refer to 23. *Procedures for Adverse Events* and 24. *Evaluation of Adverse Events* for information that must be reported in case of serious adverse events.

If a subject is transported to another medical institution due to an event, the following information will be obtained through cooperation from the subject or family, etc., then entered into medical records and used as reference materials.

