### **7.1.2. Serious adverse events**

Serious adverse events are adverse events for which any of the following apply:

1) Fatal

2) Life-threatening

The term "life-threatening" refers to an event in which the subject was at risk of death at the time of the adverse event; it does not refer to an event which hypothetically might have caused death if it were more severe.

3) Requires hospitalization or prolongation of existing hospitalization for treatment

4) Results in persistent or significant disability/incapacity

5) Is a congenital anomaly/birth defect

6) Other conditions, i.e., a medically important event for which treatment is required to avoid risks or items 1)–5) above, even if the event is not immediately life-threatening, or resulting in death or hospitalization. Examples include bronchospasm requiring intensive care in emergency rooms etc.; blood disorder or convulsions not leading to hospitalization; and drug dependence or abuse.

Explanation of "hospitalization for treatment" for serious adverse events

"Hospitalization for treatment" is defined as hospitalization of a subject in a medical institution (usually for at least one night) for treatment of adverse events, even if no particular treatment is performed (resting cure). This does not include hospitalization for examination or treatment of the primary disease or complications not aggravated from pre-observation conditions; hospitalization for convenience or personal reasons not intended to treat adverse events; and hospitalization for treatment or examination that was already scheduled prior to the first visit.

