#### **23.2.5. SAE reporting to IDMC and other collaborating clinical study institutions for the study**

The analysis officers in charge of the interim analysis in the data center will make lists and tabulate SAEs reported according to 23.2.2. *Immediate reporting procedures*, then report to IDMC members every month. Details were described in “The Independent Data Monitoring Committee Procedure Manual”. Instead of SAEs reporting to investigators at other site as prescribed by the *Ethical Guidelines for Clinical Studies*, the analysis officer will report the listed SAEs to all investigators.

These reports will not include information on treatment group in order to avoid various biases.

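### Section 23.2.2 limits the funding company to DAPT-group SAEs in item 2 but not in items 1 and 3, so SAPT cases could be identified by subtraction; section 23.2.5 appears to withhold treatment group from the IDMC's monthly lists

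*Supplement*

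**What the plan says.** All references are to protocol v1.3.

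**What must be reported.** Section 23.2.1 requires immediate reporting of "All SAEs occurring during the observation period, regardless of their relationship with the study drug". Both arms are covered, because section 5.1.1 states that "Cilostazol, aspirin and clopidogrel are referred to below as study drugs". Endpoint events are not exempt: section 6.3.3 refers to sections 23 and 24 "for information that must be reported in case of serious adverse events". The seriousness criteria in section 7.1.2 include "Requires hospitalization or prolongation of existing hospitalization for treatment", as well as lasting or significant disability.

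**Who receives it.** Section 23.2.2 has three items.
- Item 1: the investigator enters the SAE at once into the EDC system, "which will report relevant information to the study sponsor and Otsuka Pharmaceutical co., Ltd".
- Item 2: a detailed report follows and goes through the EDC to the sponsor. For the company the text adds that "the information of DAPT group will be reported to PV department (pharmacovigilance division").
- Item 3: further records on a reported SAE go to the company, among others, on request.

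**What the IDMC receives.** Under section 23.2.5, the interim-analysis officers in the data center send SAE lists to the IDMC every month, and listed SAEs also go to all investigators. The section ends: "These reports will not include information on treatment group in order to avoid various biases". Section 11.4.2 separately provides by-treatment tabulations at every safety interim review.

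**Confidentiality.** The only duty stated for interim data is in section 11.4.2: "Then the officers and member of IDMC bear the duty to maintain the confidentiality of any information in the review".

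**The concern.** Item 2 restricts what the company's pharmacovigilance department receives, and item 1 makes the restriction ineffective. The DAPT feed has a clear purpose: section 23.2.4 makes the company responsible for reporting unexpected reactions due to cilostazol. No such purpose is given for SAPT cases, since the same section assigns unexpected reactions to other drugs to the study center directors.

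No blinding of treatment is described, and investigators learn the allocation at enrolment (section 4.1). What needs protecting before database lock is therefore the accumulating comparison between arms. The company funds the trial (section 15) and owns its data (section 22), but section 11.4.2 does not name it among those bound to confidentiality.

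The IDMC point runs the other way. Section 27.3 lists monthly safety monitoring as an activity distinct from the yearly review. Section 11.4.1 sets no stopping criteria for safety and relies on the committee's judgement of incidence rates. Lists without treatment group give it nothing to compare.

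**Working it through.** **Step 1: trace the two streams to the company.**

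| | Item 1 | Item 2 |
|---|---|---|
| Timing | Immediate | Detailed report, afterwards |
| Arms | Both (no limit stated) | DAPT only |
| Recipient | The company, no unit named | Its pharmacovigilance department |
| Content | Undefined | Information on the DAPT group |

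Item 1 does not say whether treatment group is included. If it is, the arm is visible directly. If it is not, all SAEs (item 1) minus DAPT SAEs (item 2) leaves the SAPT SAEs, provided that someone matches the cases. With 2,000 per group (section 10.1) the denominators are nearly equal, so counts alone would be informative. Item 3 is a further route, because it is not limited by arm.

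**Step 2: check the plan's rates before using them.** Section 11.1 gives 4% and 2.8% per year, two-sided 5%, 80% power, 2.5 years of enrolment and 3.5 years in total. Schoenfeld's formula with hazard ratio 0.7 gives 4 × (1.960 + 0.842)² / (ln 0.7)² = 247 events. With exponential hazards of 0.04 and 0.028, uniform accrual and no dropout, the mean event probability is 0.0733. Then 247 / 0.0733 / 2 is about 1,686 per group, against the stated 1,688. The rates are used as hazards below. The sample size itself is not in question.

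**Step 3: how many primary events could be involved.** The person-years are those of section 11.4.1, split equally.
- Interim, 4,000 person-years: 2,000 × 0.04 = 80 SAPT; 2,000 × 0.028 = 56 DAPT; total 136.
- End, 8,000 person-years: 4,000 × 0.04 = 160 SAPT; 4,000 × 0.028 = 112 DAPT; total 272.

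The documents do not say what share of recurrences would be reported as SAEs. Assuming 80% to 100%, the totals are 109 to 136 at the interim and 218 to 272 at the end.

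**Step 4: what such counts would reveal.** The expected z is √(events/4) × |ln 0.7|, with |ln 0.7| = 0.357.
- Interim: √(136/4) × 0.357 = 2.1; with 109 events, 1.9.
- End: √(272/4) × 0.357 = 2.9; with 218 events, 2.6.

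If the assumed effect were true, the counts would be informative about the primary comparison well before database lock.

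**Step 5: read section 23.2.5.** Its heading names both the IDMC and the other institutions. Its body describes the IDMC lists and then the investigator lists, and the closing sentence refers to these reports without distinction. The natural reading covers both. By-treatment data then reach the IDMC at the safety reviews, in principle yearly, and at the single efficacy and safety review, but not in the months between.

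**The case against.** **The subtraction is an inference.** The content of item 1 is undefined, no text says that the same people receive both streams, and matching is not described. If both streams end in the pharmacovigilance department, this is close to ordinary manufacturer safety reporting. That stands, and it limits the point to what the routing permits. It does not remove the inconsistency, because no text confines the item 1 information to that department.

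**It looks like incomplete redrafting.** The change to v1.2 narrowed item 2 and moved the monthly lists from the company to the data center, so the direction was towards less company access. That is plausible. It makes the point one of reconciling the text, and it implies no intent.

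**A reader might infer that the company followed results by arm, or that this influenced the one-year extension in v1.3.** The documents do not support either. Revisions rest with the principal investigator, with approval by the Protocol Authoring Committee and ethics review of significant changes (section 18). Early stopping rests with the principal investigator on IDMC advice (section 19.4). The target of 4,000 did not change, and section 10.2 runs enrolment until that target is met.

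**A reader might also infer that the IDMC works without treatment group altogether.** It does not, since section 11.4.2 gives it by-treatment tabulations at every safety review. The closing sentence of section 23.2.5 could also be meant for the investigator lists alone, where its reason of avoiding bias fits best, and the IDMC Procedure Manual is not shown. On that reading there is no gap, but the sentence still needs clarifying.

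**Conclusion.** The point holds as an inconsistency with a stated consequence. Item 2 of section 23.2.2 restricts the company to DAPT cases; items 1 and 3 do not, and no firewall is described. SAPT cases, including strokes and bleeds reported as SAEs, could therefore be identified. The potential exposure is about 109 to 136 ischaemic strokes at 4,000 person-years and 218 to 272 at 8,000. These figures rest on the plan's rates, equal person-years per arm and an assumed 80% to 100% reported as SAEs. They describe what the routing would allow and do not measure any bias that occurred.

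The second part holds on the natural reading of section 23.2.5. Between by-treatment reviews, an interval of up to about 12 months if the yearly schedule is kept and no other review falls in between, the IDMC's monthly lists cannot show an excess in one arm.

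Both passages should be corrected. Doing so protects against operational bias and strengthens safety monitoring. It calls no result into question.

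**What to change.** **Section 23.2.2, items 1 and 3.** Keep the sponsor as recipient of all SAEs. Restrict what the company receives, or may request, to DAPT-group cases sent to its pharmacovigilance unit. Removing the company from item 1 altogether would go too far: item 1 is its immediate notice of DAPT cases, on which the cilostazol reporting in section 23.2.4 relies, and item 3 would remain open.

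**Firewall.** State that by-arm counts of endpoint events do not leave the pharmacovigilance unit before database lock. This is needed even with a DAPT-only stream, which by itself shows the count in one arm.

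**Section 23.2.5.** Limit the sentence on withholding treatment group to the investigator lists. State that the IDMC receives its monthly lists by arm, prepared by the interim-analysis officers, who already tabulate by treatment under section 11.4.2. Align the IDMC Procedure Manual.

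**Cost.** A few sentences and a change to EDC alert routing. Immediate notice of cilostazol cases is kept. The small downside is that the IDMC sees small by-arm counts each month.
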